### **Research Structure:**

In this single-arm pilot program, we will enroll 100 AA male participants from the annual AAMWI walk/health fair who have poor or average cardiovascular health ( $< 4$  LS7 metrics in the ideal range) with the goal of accomplishing aims exhibited in Figure 2. Our intervention involves two components: a community health worker (CHW) and peer team. Each participant will be assigned to a CHW and grouped into a team of 10 participants based on participant proximity to a central meeting location (total 10 teams). The CHW will assist in activating individual participants to engage in primary care, social support services, and enrollment in ResearchMatch. Within the teams, health coaches will assist the study team in implementing the community-based lifestyle intervention spanning LS7 principles and ResearchMatch, as shown in Figure 2 below.

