#### Secondary Outcomes (Pre-Post):

## Research Protocol: Creating Healthier Communities – AAMWI & OSU

- Prevalence of participants with a primary care provider
  - Change in social and patient activation needs
  - Change in cardiovascular health as per American Heart Association LS7 Metrics including blood pressure, cholesterol, glucose, smoking, body mass index, physical activity and dietary intake
  - Prevalence of participants participating in OSU ResearchMatch.
- i. We will measure feasibility via the study procedure logs (i.e., study enrollment and study contact completion).

We will assess protocol acceptability (satisfaction, usefulness, and plans and change of behavior to apply health promotion strategies). At the end of each program session, participants will complete a process evaluation via exit survey reviewed by stakeholders. We will use open-ended items to evaluate each participant's SMART goals and progress toward those goals. We will also inquire about what and how the participants like, dislike, and recommend intervention improvement. Specific questions will be: 1) What are your SMART Goals this week? 2) Do you have concerns about your ability to meet the goal(s) you set? If so, list your concern(s). 3) Have you changed your behavior as a result of the intervention? If so, how? 4) On a scale of 0 to 10 (with 0 being not at all satisfied and 10 being completely satisfied) how satisfied are you with this session? 5) On a scale of 0 to 10 (with 0 being not at all useful and 10 being most useful), how useful do you find this session? 6) What was the most useful part of this session? 7) Do you have any additional comments or suggestions?

- ii. Validated Questionnaires will be assessed prior to intervention, 12 weeks (mid-point) and post intervention (24 weeks)

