- Centers for Medicare and Medicaid Services Accountable Health Communities Health-Related Social Needs Screening Tool - The Centers for Medicare & Medicaid Services (CMS) Accountable Health Communities Model, tested by the Center for Medicare and Medicaid Innovation, addresses the critical gap between clinical care and community services in the current health care delivery system by testing whether systematically identifying and addressing the health-related social needs of Medicare and Medicaid beneficiaries impacts their total health care costs and improves health. The questionnaire includes 26 questions addressing living situation, food security, transportation, utilities, safety, financial strain, employment, family and community support, education, physical activity, substance abuse, mental health and disabilities.
  - Insignia Health Patient Activation Measure - The Patient Activation Measure (PAM) contains 13 items, segmenting individuals into one of four activation levels along an empirically derived 100-point scale. The four activation levels are 1) disengaged and overwhelmed, 2) becoming aware, but still struggling; 3) taking action and 4) maintaining behaviors and pushing further. Each level provides insight into an extensive array of health-related characteristics, including attitudes, motivators, and behaviors. Individuals in the lowest activation level do not yet understand the importance of their role in managing their own health, and

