#### **Primary outcome: Feasibility and Acceptability**

Descriptive statistics will be used to summarize quantitative data, including subject recruitment rate, retention rate, the degree of intervention adherence, and the average rating of the satisfaction of the intervention, including the content, length, and dose of the intervention. We will conduct content analyses on qualitative data obtained from verbatim transcripts of sessions and open-ended items of the battery. We will independently explore the data for patterns and significant statements that address intervention acceptability in NVivo 12 software. The research team will discuss, compare, and reduce codes iteratively until inter-coder agreement is met ( $\kappa > 80\%$ ). Finally, we will use matrices to compare qualitative and quantitative acceptability data from the questionnaires. A mixed methods approach will lead to better understanding of how the intervention is perceived, along with which/how strategies affect outcomes in patient engagement and health-related outcomes. We expect that intervention is feasible, and AA men will perceive it as acceptable; however, findings may indicate further need to adapt the intervention (e.g., length of intervention).

Secondary outcomes: 1) prevalence of participants with a primary care provider, change in social and patient activation needs; 2) Changes in cardiovascular health as per American Heart Association LS7 Metrics including blood pressure, cholesterol, glucose, smoking, body mass index, physical activity and dietary intake; and 3) prevalence of participants participating in OSU ResearchMatch. For each outcome, we will use mixed-effects linear modeling for repeated measures to (a) test the fixed effect of time, intervention group, and their interaction; (b) derive within-group and between-group contrast estimates on the change from baseline at each follow-up. Within-subject random effects will be included in the model to adjust for within-subject clustering from longitudinal follow-up. We will also adjust for potential confounders by including them as fixed-effects covariates in the model.

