## **Research Protocol:**

### **Creating Healthier Communities – AAMWI & OSU**

All statistical analyses will be performed using either SAS 9.4 or the most current version (SAS Institute, Inc., Cary, NC) or Stata 15 or the most current version (Stata Corporation, College Station, TX). Descriptive statistics (mean, median, standard deviation, proportions, etc.) of each of the collected variables will be estimated overall.

Sample Size and Power Analysis: This is a pilot study so sample size and power calculations were not performed. We will use data from this pilot study to solidify protocol parameters and estimate the degree of attrition that is considered in sample size and power calculation for a full-scale randomized controlled trial.

Missing Data: We expect missing data, for the post-intervention measures, where we expect a 10% attrition rate. We will carefully examine the pattern of the missing data and impute missing data via multiple imputation methods if missing completely at random (MCAR) mechanism is present. The mixed effects modeling approach described earlier allows for data missing at random (MAR). If the pattern of missing data indicates the potential missing not at random (MNAR), pattern-mixture modeling will be used. The robustness of findings under MCAR, MAR, and MNAR mechanisms will be evaluated.

Heterogeneity of Treatment Effect (HTE): To determine if there is HTE, we will extend our analysis models to include statistical interactions between participant factors and treatment and perform Wald tests of the interaction effect. Potential interaction factors include age, income, education level, neighborhood SES, and food insecurity. These analyses will be considered exploratory and thus no additional adjustment of p-values will be undertaken.

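### Food insecurity is listed as an effect modifier and is also part of the social-needs score, so for that one outcome the exploratory interaction test is biased by regression to the mean

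*Protocol*

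**What the plan says.** Four parts of the protocol bear on this.

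- **Heterogeneity of Treatment Effect paragraph.** The analysis models are to be extended with interactions between participant factors and treatment, each judged by a Wald test. On the factors: "Potential interaction factors include age, income, education level, neighborhood SES, and food insecurity". No outcome is exempted. The analyses are called exploratory, and p-values are not adjusted.
- **Secondary outcomes, analysis text.** The models being extended are these: "For each outcome, we will use mixed-effects linear modeling for repeated measures".
- **Secondary Outcomes (Pre-Post).** The list of outcomes includes "Change in social and patient activation needs".
- **Outcome Measures, item ii.** Social needs are measured with the Accountable Health Communities screening tool before the intervention, at 12 weeks and at 24 weeks. Its description reads: "The questionnaire includes 26 questions addressing living situation, food security, transportation, utilities, safety, financial strain, employment, family and community support, education", and it goes on to four further areas, which makes 13. No other listed instrument is described as measuring food security.

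The design comes from Research Structure: "In this single-arm pilot program", and "we will enroll 100 AA male participants from the annual AAMWI walk/health fair". The Missing Data paragraph adds "we expect a 10% attrition rate" for the post-intervention measures.

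**The concern.** Read together, these passages let a baseline characteristic be tested as a modifier of change in a score that contains that same characteristic. A man recorded as food insecure at baseline can only stay the same or improve on the food item. A man recorded as food secure can only stay the same or worsen. Ordinary inconsistency in answers between visits is therefore enough to separate the two groups.

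A control arm would show the same drift and cancel it in a factor-by-treatment contrast. This trial has none, so the drift goes straight into the factor-by-time term.

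The bias has a known direction: it always favours the reading that food-insecure men gained more. For a programme that navigates men to social support, that is a plausible and welcome result, and so one that is easily believed.

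**Working it through.** **No figure to reproduce.** The protocol reports no power calculation, significance level or scoring rule for this tool. What follows tests the consequence of the plan under stated assumptions.

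**Inputs from the protocol.** One arm; 100 enrolled; 10% attrition, so 100 × 0.90 = 90 with post-intervention data; three visits; a linear mixed model with a Wald test; 13 named areas in the tool.

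**Assumptions, not in the protocol.** The factor is the baseline food item. The score is the count of positive areas, K = 13, or K = 5 for a shorter score. Prevalence p of a need is 20% to 35% per area. Test-retest kappa is 0.5 to 0.8, extended to 0.9 and 0.95. The level is 5% two-sided. Nothing truly changes, and all men follow the same response process.

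**Step 1: size of the spurious difference.** For a yes/no item with stable prevalence p and kappa k, the expected changes on the food item are:

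- food insecure at baseline: [p + k(1 − p)] − 1 = −(1 − k)(1 − p)
- food secure at baseline: p(1 − k) − 0 = +p(1 − k)
- difference: −(1 − k)(1 − p) − p(1 − k) = −(1 − k)

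With p = 0.30 and k = 0.65 this is −0.245 − 0.105 = −0.35 of one need. Over k = 0.5, 0.65 and 0.8 it is −0.50, −0.35 and −0.20. Simulation gives the same values.

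**Step 2: rejection rate by hand.** Take independent areas, p = 0.30, k = 0.65 and 90 men, so 27 are food insecure and 63 food secure. The variance of change per area is 2p(1 − p)(1 − k) = 2 × 0.21 × 0.35 = 0.147.

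| | K = 13 | K = 5 |
|---|---|---|
| SD of change, √(0.147K) | 1.382 | 0.857 |
| SE of difference, SD × √(1/27 + 1/63) = SD × 0.230 | 0.318 | 0.197 |
| Expected z, 0.35/SE | 1.10 | 1.77 |
| Rejection at 5% two-sided | about 20% | about 43% |

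A change-score t-test simulated under the same conditions rejects in 19% and 43% of trials.

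**Step 3: the planned test.** Simulated rejection rates with no real difference (random-intercept model, categorical time, 2-df Wald test of factor by time):

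| Kappa | 13 areas, 90 completers | 13 areas, 100 men with attrition | 5 areas, 90 completers | 5 areas, 100 men with attrition |
|---|---|---|---|---|
| 0.5 | 25% to 30% | 28% | about 60% | 62% |
| 0.65 | 20% to 28% | 22% | 47% to 49% | 43% |
| 0.8 | 15% to 19% | 13% | 30% to 34% | 28% |
| 0.9 | 12% | not run | 19% | not run |
| 0.95 | 9% | not run | 12% | not run |

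The ranges for kappa 0.5 to 0.8 cover prevalence 20% and 35%. The attrition columns and the last two rows use 30%. The attrition columns rest on 250 replicates each, so they carry a few points of simulation error. A change-score t-test at 25% prevalence gives 13% to 26% (13 areas) and 26% to 57% (5 areas) over kappa 0.8 to 0.5. If the food area were analysed alone, the Wald test would reject in 88% to 100% of trials over that kappa range.

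**Step 4: the overlap removed.** At kappa 0.65 and prevalence 30%, with the food item taken out of the score, the Wald test rejects in 7.1% (13 areas) and 7.7% (5 areas). The t-test rejects in about 5% to 6%. Taking food insecurity from a separate measurement occasion gives the same Wald rates, 7.1% and 7.7%. Nearly all of the excess therefore comes from the overlap. The remaining 2 to 3 points in the Wald test do not.

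**The case against.** **The pairing is not spelled out.** The factors are called potential, they are not matched to outcomes, and the source and timing of the food-insecurity variable are not given. A statistical analysis plan could settle all of this. That stands as a limit: use of the tool's baseline answer is an inference from the absence of any other listed measure. The protocol does, however, fix a factor, a set of models covering every secondary outcome and a test. Followed as written, these include the faulty pairing.

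**The interaction as written cannot be fitted.** A factor-by-treatment term has no meaning with one arm. This is correct, and it is a wider defect of the analysis text. The figures here apply to factor by time, the only version that can be run.

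**The size rests on assumptions.** This stands. Scoring, prevalence, kappa and level are all assumed, and with a very stable food item and 13 areas the inflation is modest. The direction of the bias does not depend on those values.

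**It is exploratory.** The label limits the consequence, and the protocol uses it to justify leaving p-values unadjusted. It does not deal with a test biased in a known direction, and adjusting p-values would not remove that bias.

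**Two stronger readings are not supported.** A reader might infer that income and education level have the same fault, since the tool covers education and financial strain. The mechanism requires factor and outcome to share the same noisy baseline answer. The Sources of Materials section names demographics separately from surveys, so these factors may be collected outside the tool, and their effect was not computed. A reader might also infer that a false subgroup lead would be carried into the follow-on trial. The protocol says the pilot will settle protocol parameters and estimate attrition, and it does not mention subgroup findings.

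**Conclusion.** The point holds for one pairing only: food insecurity as a modifier of change in social needs. Patient activation and the Life's Simple 7 metrics do not contain the factor and are not affected, and the primary feasibility and acceptability outcomes are not touched.

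For that pairing, if the factor is the tool's baseline answer, the test shows a spurious advantage for food-insecure men of about (1 − kappa) of one need. At a nominal 5% level, with a count score and prevalence of 20% to 35%, false positives are about 13% to 30% for 13 areas and 26% to 62% for 5 areas over kappa 0.8 to 0.5. For 13 areas they are about 9% to 12% at kappa 0.95 to 0.9. Without the food item they are about 5% to 8%. All these rates are for no real change over time. It would go too far to say that the test is always wrong far more often than 5%, because that depends on scoring and repeatability, which the protocol does not give.

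This is a fault in an exploratory analysis of a secondary outcome. It should be corrected because the correction is simple and the bias points towards an attractive conclusion.

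**What to change.** Add to the heterogeneity paragraph: *For the social-needs outcome, food insecurity is tested as a modifier only with the food-security items removed from the score; change on the food-security items is reported descriptively.* Apply the same rule to education or income only if that factor is taken from the tool's own items. The same edit should say that, with one arm, the interaction tested is factor by time.

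The cost is one sentence and one alternative score, with no new data, visits or participants. There is a small downside: the test no longer captures relief of food need itself, which navigation may well aim at. The descriptive report keeps that information visible, without a p-value that regression to the mean would distort.

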#### **Confidentiality**

Demographic, screening and survey data will be stored electronically behind the OSUWMC firewall in REDCap. Only the PI, co-investigators and the research assistants working on the project will have access to the data. All computers that will be used to store data will be password protected behind the OSUWMC. Electronic copies of forms will be stored on a secure dedicated server with appropriate firewalls. The system will use 128-bit encryption (SSL certificate) to transfer data between the machines. This technology is the same as that used for online e-commerce applications to protect consumer information such as name, address, and credit card details. Servers are scanned for viruses and systems are in-place to detect attempts at unauthorized entry. The data base server is backed up 3 times a day internally. Personal information will be stored confidentially for the minimum required amount of time after study completion.

#### **Protection of Human Subjects**

This human subjects research meets the definition of a clinical trial. We will not recruit from any vulnerable populations for this study.

#### **I. Sources of Materials**

Research Material obtained from living human subjects will include the following:

a. Finger stick samples: Cholesterol and Glucose, Pre-intervention, 12-weeks and Post-intervention

## **Research Protocol: Creating Healthier Communities – AAMWI & OSU**

b. Data: Demographics and surveys completed during the course of the study and the anthropometric and clinical information collected (blood pressure, height, weight, etc.) pre-mid-post study.

### **Potential Risks:**

1. Finger Stick cholesterol and glucose done at intervention site

#### **Likely / Common**

##### *Mild*

- Discomfort during finger prick
- Anxiety before and during finger prick
- Bleeding
- Bruising

The total amount of blood that will be collected for this entire research study (over 12 months) is approximately < 5 ml of blood. However, the tests are spread out over time, therefore, the risk of experiencing side effects is minimized.

##### *Rare*

- Infection at the site of blood drawing.

2. Injury during class i.e. burns or cuts – same procedure as #2.

### **Loss of confidentiality:**

There is a potential risk that confidential information about the subject may be accidentally disclosed.

### **Confidentiality:**

The research team will do everything we can to protect participant's privacy. Upon entry into the study, participants will be assigned a subject ID number. All of the study-related documents will be coded with this ID number so identities will be kept confidential. Study records will be stored in a locked area and only the study team will have access to them.

The research team will follow state and federal laws and may share information, only as necessary, with:

- Government representatives, (including the Office for Human Research Protections or the Food and Drug Administration) to complete federal or state responsibilities
- Hospital or University representatives to complete Hospital or University responsibilities
- Primary care physician if a medical condition that needs urgent attention is discovered
- The Research Subject Advocate at the CRU
- Regulatory agencies in other countries
- Other research laboratories working with us on this and other similar studies. When possible, the research team will make sure information cannot be linked to a specific individual.

### **Monitoring the Safety of Individual Participants**

A. A research team member will be present during all testing procedures to monitor the safety of the individuals. A study team member will review any adverse events that may occur after or between visits. The primary investigator and co-investigators will monitor study progress on a weekly basis. Regular check-ins by the Principal Investigator

## **Research Protocol: Creating Healthier Communities – AAMWI & OSU**

will be conducted with study team members to discuss any difficulties. All unanticipated problems will be reported to the IRB promptly. All events will be reviewed monthly by the PI and co-investigators. All serious adverse events (e.g. death or life-threatening adverse event) will be reported to the OSU Biomedical IRB verbally within 24 hours and written within 7 days of the event. Protocol deviations that may be expected to recur will also be reported immediately. Should there be a serious adverse event deemed related to the investigative treatment that increases the risk to participants, the study will be stopped, an investigation conducted, and findings generated before the study is resumed. These findings will be shared immediately with the IRB.

### **B. Description of anticipated adverse events (AE)**

Definition of an AE: Any untoward medical occurrence in a subject in the intervention group, which could include a serious musculoskeletal injury requiring medical attention. All adverse events will be recorded in the study database including the following information:

1. the severity grade (mild, moderate, severe)
2. its relationship to the intervention
3. its duration (start and end dates or if continuing at final exam)
4. whether it constitutes a serious adverse event (SAE)

A SAE is any untoward medical occurrence that at any dose:

- results in death,
- is life-threatening,
- requires inpatient hospitalization or prolongation of existing hospitalization,
- results in persistent or significant disability/incapacity,
- is a congenital anomaly/birth defect,
- is otherwise a significant medical event.

Any SAE, irrespective of causality, occurring after the subject has provided informed consent and until four weeks after the subject has stopped study participation must be reported unless otherwise stated in the protocol. SAEs occurring after four weeks from ending study participation should only be reported if considered by the Investigator attributable to the exposure to the investigational drug(s) during the trial period. This includes the period in which the study protocol interferes with the standard medical treatment given to a subject, even if study treatment has not yet started (e.g. withdrawal of previous treatment during washout period, change in treatment to a fixed dose of concomitant medication).

